**Executive summary**

Belén, a community of extreme poverty in Peru, has listed intestinal parasites such as soil-transmitted helminths (STH) (*Ascaris, Trichuris*, and hookworm) among their top-five health priorities during recent multidisciplinary participatory workshops [1]. Furthermore, a school survey conducted in 2006 in this community demonstrated a very high prevalence of STH infections, with 86% of Grade 5 students infected with one or more species of parasites [2]. To efficiently control this disease cluster, WHO, PAHO, and others recommend the inclusion of an education strategy in school-based deworming programs [3-6]. However, the effectiveness of such a strategy on the rate of STH re-infection and on education indicators, such as absenteeism, remains to be fully understood. The proposed research aims to evaluate the effectiveness of a post-deworming education intervention targeted to Grade 5 school children enrolled in Belén’s schools using a cluster-randomized trial design. Results will be used to inform school-based deworming programs in Peru and other similar endemic areas in Latin America and, indeed, around the world.

**Context of the present protocol submission**

The present submission details a 4-month project based entirely in Peru, which will be conducted within a larger 5-year research program (2006-2011) already funded by the CIHR (RI-MUHC account 6360). The 5-year project is an Interdisciplinary Capacity Enhancement (ICE) grant. As such, the ICE project included overall objectives only. The plan was to develop specific projects within the ICE grant in conjunction with local co-investigators and collaborators, and the local community. Ethics review was not required for the overall 5-year project. Instead, as projects would be developed, they would individually be submitted for appropriate ethics approval, both in Peru and in Canada. Ethics approval from Peruvian Health officials for the current project is underway. English and Spanish versions of the parents/tutor informed consent form, the students assent form and the questionnaire are attached in the Annex.

**Location of study conduct**

The Belén district of Iquitos is located on the banks of the Itaya/Amazon River in Peru. Due to the propensity of this area for seasonal flooding, the houses are constructed on wooden stilts or on floating platforms. Most inhabitants do not have access to reliable potable water for drinking or improved sanitation systems. Human waste contaminates the water directly from floating latrines or indirectly from land-based latrines, leading to a state of extensive fecal contamination.

**Study rationale**

Because of the very high prevalence of STH in Grade 5 school children in Belén, Peru, efficient and sustainable control methods are needed. There has been no systematic review on the proposed research topic. Few studies have investigated the effectiveness of a post-deworming education intervention on STH (*Ascaris, Trichuris*, and/or hookworm) prevalence or re-infection rates, or on absenteeism, and only five studies have previously examined school-based education interventions. These studies yielded mixed evidence and results are difficult to interpret because of methodological limitations. Therefore, in this current state of scientific equipoise, our proposed cluster-randomized trial is needed to inform both policy and practice related to school-based deworming programs in Peru and in other endemic countries.

**Scientific background**

Globally, STH (*Ascaris, Trichuris*, and hookworm) infections are one of the most important neglected disease clusters worldwide as they affect over two billion people and they contribute significant morbidity and disability, especially in the high risk group of school-age children [7]. STH are the leading cause of physical and intellectual growth and development delays and impairment of children in endemic areas [8-10]. Furthermore, it is in school-age children that peak prevalences and peak intensities of STH infections occur [11]. The World Health Organization (WHO), UNICEF, and the World Bank, among others, recommend establishing school-based deworming programs as the most cost-effective means to combat the adverse health outcomes of these parasitic diseases. The rationale for these school-based interventions is to reduce the highest STH-attributable burden of disease (by treating the highest risk group of school-age children). By doing so, this intervention also reduces environmental contamination, and consequently, infection in the wider community [12]. Further, school-based deworming programs have been shown to be “a crucial, and neglected, step towards improving public health and to reaching several of the Millennium Development Goals” (MDG) [13, 14], which call for concerted improvements in poverty reduction, nutritional status, education, gender equality, and environmental degradation. For example, treatment with deworming drugs (eg. albendazole) led to a 25% reduction in primary school absenteeism in Kenya [15], prevented 82% of stunting and was associated with a 35% weight gain among children in Indian slums [16]. Despite their usefulness, school-based deworming programs have several constraints: many endemic communities don’t have them (only 64 of 130 endemic countries reported any school-based deworming activity at all in 2006); positive effects are temporary (in the absence of any behavioural or environmental change, due to re-infection) [17], thereby requiring repeated treatment; and deworming programs incur costs, even if the drug itself is free of charge or of low cost [3, 18].

The inclusion of a health education strategy in school-based deworming programs is therefore recommended as a way to improve their effectiveness [3-6, 19]. The specific objectives of the health education strategy are to prevent re-infection and improve school effects, like absenteeism. STH infections being acquired through the fecal-oral transmission route (*Ascaris* and *Trichuris*) or contact with contaminated soil (hookworm), the approach of health education programs is to promote behavioural changes that would reduce exposure and risk of contamination. Other advantages of these education programs is that they can reduce the cost of deworming, increase the level of overall health knowledge within the community, reduce morbidity attributable to STH infections and promote optimal productivity as adults [6, 20, 21].

A literature review on the efficacy or effectiveness of school-based health education interventions on the prevalence or infection rates of STH infections retrieved only five studies, none of them from Latin America. An annotated summary of these studies demonstrates a state of scientific equipoise regarding our proposed research question (Table 1). Furthermore, evidence from these studies is difficult to interpret and to generalize because: some did not have appropriate comparison groups; the health education intervention was sometimes implemented together with environmental sanitation programs or other interventions; there was often no statistical adjustment for confounders nor any correction for within-school clustering of students; some had low sample sizes, targeted different age groups, had variable follow-up periods and were often only descriptive in nature. The cumulative evidence is therefore equivocal, not only because some studies showed a negative effect, an absence of effect, or a positive effect of the health education intervention on STH prevalence or re-infection rates, but also because the methodological basis for this evidence is less than rigorous.

Table 1: Annotated review of studies conducted on the efficacy or effectiveness of health education intervention on STH prevalence or re-infection rates

| **Location (Year)** | **Study Design** | **# schools** | **# children** | **Limitations** | **Results** | **Ref.** |
| --- | --- | --- | --- | --- | --- | --- |
| China  (1997) | Observational | 6 schools  (4 received the intervention) | 6,188 | - No adjustment for school clustering  - No measure of effect reported  - Intervention consisted of a health intervention plus environmental sanitation | Schools with the environmental sanitation and health intervention had lower re-infection rates. | [22] |
| Indonesia  (2005) | Observational | 45 schools  (5 received the intervention) | 3,463 | - Descriptive study  - No statistical analysis  - No adjustment for potential individual confounders | Schools receiving the health education intervention had lower prevalence at 7 months | [23] |
| Indonesia  (1998) | Factorial RCT | 5 schools  (4 treated and 1 control) | 336 | - Individual confounders not taken into account  - Low sample size | No effect differences were found between the ‘deworming group’ and the ‘deworming plus education’ group | [24] |
| Seychelles  (1994) | Observational | 23 schools  (all received the intervention) | 1,244 | - No comparison group  - No statistical analysis  - Intervention consisted of health education, environmental sanitation, and deworming | Deworming, environmental sanitation, and health education reduces the prevalence of STH | [25] |
| Thailand  (2004) | Observational | 4 schools  (all received the intervention) | 428 | - No comparison group  - Low sample size | Prevalence of STH was higher at the end of the health education intervention compared to baseline | [26] |

**Objectives**

**Primary**

The primary objective is to determine the effectiveness of a school-based health hygiene education intervention to reduce re-infection by STH after a routine deworming intervention.

**Secondary**

The following secondary research objectives will also be addressed: i) to determine intervention effects on absenteeism rates; ii) to assess gender-specific determinants of STH infection, re-infection and absenteeism rates; iii) to measure STH species-specific cure rates and egg reduction rates; and iv) to examine behavioural and social determinants of STH infection, re-infection and absenteeism rates.

**Methods**

**Study design**

A prospective cluster-randomized controlled trial design will be used (Figure 1). Schools will be randomly allocated to one of the two arms using a stratified randomization technique (by school size). Because the total number of students enrolled in Grade 5 varies from 20 to more than 200 per school, the stratified design will ensure a balanced proportion of children in each of the two arms. A simple baseline questionnaire will be administered to all Grade 5 students to collect information on gender-specific risk factors and to evaluate the level of knowledge regarding STH infections. Each child will be weighed and measured (for anthropometric measures), and a stool specimen will be collected and examined for STH eggs (to estimate STH infection rates and intensity). The health hygiene education intervention will begin immediately after the routine deworming program in schools in the intervention arm. Schools in the control arm will follow their standard curriculum. (These schools will be offered the health hygiene education intervention after the 4-month follow-up period.)

Two weeks after the deworming, an efficacy assessment will be undertaken in a sub-sample of 300 previously-infected children (ie. Stool specimens will be collected to estimate cure rates for each STH. This is needed to provide a correction factor in the data analyses.). At the end of the 4-month follow-up study period, the baseline questionnaire will be re-administered to all children in both arms, the children will be weighed and measured, and re-infection rates will be assessed by collecting a stool specimen from each child. Absenteeism rates, based on routine school records, will be assessed from baseline to the end of the follow-up period. An intention-to-treat analysis will be used to compare outcomes in the two arms.

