**Sample size justification**

Based on our survey of schools in Belén, 18 schools are eligible and have already demonstrated an interest in participating in the study. They have a total of 1438 students enrolled in Grade 5 (Table 2). Power calculations are based on the formula for logistic regression with a single binary covariate (i.e. the education intervention) and the Wald test was used as the basis for computations [39]. Based on our past parasitological Belén school surveys a response rate of 80.6% is expected [2]. A 5% loss to follow-up is also assumed during the 4-month period. Thus, we estimate a sample size of 1101 participating students, distributed in the 18 schools.

In addition, the power calculations must take into account within-school clustering. The intraclass correlation coefficient (ICC) represents the proportion of the total variance that is accounted for by between-cluster rather than within-cluster variation and can be used to calculate the Effective Sample Size (ESS). Because we could not find any reported ICC of within-school clustering of STH re-infection in the literature, we re-analysed the original database of [name] et al. [2], which contained the parasitological results of 1074 Belén students, and calculated the within-school ICC of STH prevalence (as an estimation of ICC of re-infection rates). The ICC was calculated using STH prevalence as the outcome and the school as the grouping factor, while adjusting for age, sex, and the school ecological zone (floodplain or upland). The obtained ICC had a value of 0.028 which resulted in an ESS of 412 and an associated design effect of 2.7. Power was estimated assuming that 50% of children will be exposed to the intervention and that the re-infection rate in the control group will be 49.5%. The latter is based on the reported 3-month re-infection rate of Malaysian school-children treated with albendazole [40]. Thus, the proposed study has good power (80.3%) to detect a moderate effect (i.e., OR=1.75) and has an excellent power (93.4%) to detect a strong effect, corresponding to an OR of 2.00.

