**Planned statistical analyses**

All children in both arms will be included in the analysis (i.e., an intent-to-treat analysis). Preliminary analyses will include descriptive statistics (means and standard deviations for continuous variables; frequencies for categorical variables) for all measurements in each intervention group separately. Gender-disaggregated data will be presented in tables, whenever pertinent.

Multivariate analyses will be used to compare the post-deworming (at 4-months) STH re-infection rates between the two groups. To account for the within-school clustering, hierarchical (random effects) logistic regression models will be used [41]. The model will include important confounding variables such as gender, sex, age, school ecological zone, as well as any baseline characteristics that may not be balanced between the two groups. Subgroup analysis will be performed for boys and girls separately as well as for each of the three helminth species studied (*Ascaris*, *Trichuris*, and hookworm).

All statistical tests will be two-sided and a 0.05 level of significance will be used throughout for determination of statistical significance. Point estimates of the intervention effect with 95% confidence intervals will be presented to demonstrate the precision of the study results.

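### Schools are randomised within school-size strata, but the size stratum is not among the covariates named for the primary model

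*Protocol*

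**What the plan says.** On allocation, the Protocol (Study design) states: "Schools will be randomly allocated to one of the two arms using a stratified randomization technique (by school size". The reason given is head-count: because "the total number of students enrolled in Grade 5 varies from 20 to more than 200 per school", the Protocol says that "the stratified design will ensure a balanced proportion of children in each of the two arms". It gives neither the number of strata nor their cut-points.

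On analysis, the Protocol (Planned statistical analyses) states: "To account for the within-school clustering, hierarchical (random effects) logistic regression models will be used". On covariates it says: "The model will include important confounding variables such as gender, sex, age, school ecological zone". A further clause extends this list with a data-dependent group: "as well as any baseline characteristics that may not be balanced between the two groups". School size, or the stratum built from it, is not in that sentence. The same section sets the error rate: "All statistical tests will be two-sided and a 0.05 level of significance will be used throughout".

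On resources, Sample size justification records that "18 schools are eligible and have already demonstrated an interest in participating in the study". Its ICC of 0.028 is adjusted for age, sex and ecological zone, not for school size.

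**The concern.** When randomisation is restricted by a factor, the arms are forced to be alike on it, and the true variance of the arm difference no longer contains that factor's contribution. A model that omits the factor still counts the contribution as unexplained between-school variation. If the factor is prognostic, the estimated standard error is then larger than the design warrants. The test rejects less often than its nominal level, and power is given away.

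This matters more here than in an individually randomised trial. There are only 18 schools and the number cannot grow, so between-school variation largely determines precision. The Protocol does name its covariates, including one at school level (ecological zone), yet passes over the one used in the allocation. The clause on unbalanced baseline characteristics is unlikely to bring school size in, because stratification is there to balance it.

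**Working it through.** **The Protocol's own figures.** Inputs from Sample size justification: 1438 enrolled, 80.6% response, 5% loss, 18 schools, ICC 0.028, control re-infection 49.5%, OR 1.75, two-sided 0.05.

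- N = 1438 × 0.806 × 0.95 = 1101 (stated 1101).
- Mean school size m = 1101/18 = 61.2. Design effect = 1 + 60.2 × 0.028 = 2.68 (stated 2.7). Effective sample size (ESS) = 1101/2.68 = about 410 (stated 412).
- OR 1.75 in the protective direction turns 49.5% into 35.9%. With 206 per arm, var(log OR) = 1/(206 × 0.495 × 0.505) + 1/(206 × 0.359 × 0.641) = 0.0405, so SE = 0.201. Then ln(1.75)/0.201 = 2.78, and power = Φ(2.78 − 1.96) = 79.4% (stated 80.3%). A two-proportion formula gives about 80%.

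The stated power is reproduced to within a point. No term in it reflects stratification.

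**Effect of omitting the stratum.** The documents do not say how much between-school variance size explains, so that share, R², is assumed and varied, with zero included. Further simplifications: 18 equal-sized schools, three strata of six, and a t-test on school means as an approximation to the random-effects model.

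On a standardised scale the between-school variance is 0.028, and the within-school part of a school mean's variance is 0.972/61.2 = 0.0159.

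- True variance per school under stratified allocation: 0.028(1 − R²) + 0.0159.
- Variance that an analysis without the stratum expects to estimate: the same plus (9/8) × 0.028 × R².
- Standard-error inflation: the square root of the ratio of the second to the first.

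For R² = 0.25, true = 0.0369 and estimated = 0.0369 + 0.0079 = 0.0448, so inflation = √(0.0448/0.0369) = 1.10. The effective critical value becomes 2.12 × 1.10 = 2.34 on 16 degrees of freedom, a two-sided error of about 3.3%. The same steps give inflation of 1.04 (about 4.3%) for R² = 0.10 and 1.24 (about 1.9%) for R² = 0.50.

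A simulation of 40,000 runs per setting agrees. The arm difference was set to give 80% power under a normal approximation, which is about 75% with a t-test on 16 degrees of freedom.

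| Assumed R² | Type I error, omitted | Type I error, included | Power, omitted | Power, included | Change (points) |
|---|---|---|---|---|---|
| 0 | 5.0% | 5.0% | 75.0% | 74.2% | −0.8 |
| 0.10 | 4.3% | 4.9% | 75.0% | 76.7% | +1.7 |
| 0.25 | 3.4% | 5.1% | 75.4% | 80.8% | +5.4 |
| 0.50 | 1.7% | 4.8% | 76.9% | 88.4% | +11.5 |

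**Cost of including it.** Three strata use two school-level degrees of freedom, so the 5% critical value moves from 2.12 (16 df) to 2.14 (14 df).

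**The case against.** The best defence has three parts.

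First, the covariate list is open: it gives examples, so size is not excluded. The full list may also be settled in a statistical analysis plan, which was not available for this review. This is fair as far as it goes, and it is why the point concerns what is named rather than a contradiction. But the Protocol commits to specific terms and does not commit to the stratum.

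Second, the purpose of stratifying was to share the children out evenly. That benefit comes from the allocation and survives whatever the model contains. This stands. A reader might infer that the gain from stratifying is lost in the analysis. The documents do not support that: they claim no precision gain, and nothing in them shows that size predicts re-infection.

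Third, any error is conservative. This also stands: no bias and no excess of false positives follow, and the 80.3% is not made wrong.

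Two further inferences are tempting.

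- *That the promise to ensure balance fails.* With three assumed strata of six, the share of children in one arm can run from 39.4% to 60.6%, and 17% of allocations fall outside 45–55%. Without stratification 57% would, and nine size-matched pairs would hold the share within 47–53%. A 60:40 split lowers power only from 79.4% to 77.4%. The verb is somewhat strong for a few broad strata, but little depends on it.
- *That ecological zone should also have restricted the randomisation.* The model already adjusts for zone, and the Protocol does not list zone by school, so the benefit cannot be checked. That is a design preference, not an error.

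**Conclusion.** The point holds as a mismatch between allocation and named analysis: the randomisation stratum is missing from the covariates stated for the primary model. Its consequence is conditional. If size explains 10% to 50% of between-school variance, the test runs at about 4.3% to 1.7% instead of 5%, and 1.7 to 11.5 points of power are forgone. If size explains nothing, omission does no harm and inclusion costs about 0.8 points. These figures rest on the assumed variance shares, three equal strata, equal school sizes and a school-level approximation. No figure stated in the Protocol is wrong on this account. The case for change is the asymmetry: a small, bounded cost against a possible gain that may be considerable, with an analysis that matches the randomisation.

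**What to change.** In Planned statistical analyses, add one sentence naming the school-size stratum as a fixed effect in the primary random-effects model, with the strata exactly as applied at randomisation. That requires the number of strata and their cut-points to be written down. The cost is that sentence and one or two of the 16 school-level degrees of freedom. No change to the sample size or the power statement is needed. Softening the claim in Study design that stratification ensures balance is optional wording.

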**Health hygiene education intervention**

Lack of knowledge on the transmission and prevention methods of STH infections is common factor in affected population groups of Latin America [27]. Therefore, the specific objectives of the health hygiene education intervention are:

i) To implement a gender-specific health hygiene education strategy which will result in a sustainable intervention that encourages the pro-active role of both teachers and students.

ii) To encourage changes in attitudes and practices with the aim of keeping the level of parasite infection low, through increased knowledge.

iii) To identify modifiable gender-specific behavioural and social determinants which favour the acquisition and transmission of STH infections to inform prevention activities.

Workshops will be organized for and by Grade 5 teachers to train them on the health hygiene education strategy. The education material will be provided by the Pan American Health Organization (in Spanish) and will be adapted to the local culture. The health hygiene education intervention will take into account the gender-specific perceptions, values, social constructs, and beliefs of students and teachers relevant to STH infections in order to maximize behavioural changes. After the workshop, Grade 5 teachers will be able to implement the health hygiene education intervention in their classroom and engage their students. Bi-monthly visits with the teacher by our research team and once monthly with the class will be performed to monitor the application of the education program during the 4-month follow-up period. Specifically, the intention of the health hygiene education program is to modify key gender-specific modifiable behavioural determinants that have been shown to be associated with STH infections from our review of the literature:

i) Not using soap for hand washing [28-30]

ii) Not hand washing (no reference to the use of soap) [31-33]

iii) Eating unpeeled or unwashed fruits [31, 34]

iv) Walking barefoot [30, 33]

v) Open air defecation [33-35]

vi) General unhygienic behaviours [36]

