**Chronogram of research activities**

The following table provides the detailed schedule of all research activities, with approximate start and end dates.

|  | **2009** | | **2010** | | | | | | | | | | | |
| --- | --- | --- | --- | --- | --- | --- | --- | --- | --- | --- | --- | --- | --- | --- |
| **Activities** | November | December | January | February | March | April | May | June | July | August | September | October | November | December |
| Preliminary school visits | ✓ | ✓ |  |  |  |  |  |  |  |  |  |  |  |  |
| Ethics approval (Canada and Peru) |  | ✓ | ✓ | ✓ |  |  |  |  |  |  |  |  |  |  |
| Trial registration |  |  |  | ✓ |  |  |  |  |  |  |  |  |  |  |
| Informing health authorities; meeting all school principals |  |  |  | ✓ |  |  |  |  |  |  |  |  |  |  |
| Randomization |  |  |  | ✓ |  |  |  |  |  |  |  |  |  |  |
| Training workshops for teachers in the intervention schools |  |  |  | ✓ | ✓ |  |  |  |  |  |  |  |  |  |
| Organization of meetings with parents (informed consent) |  |  |  |  | ✓ |  |  |  |  |  |  |  |  |  |
| Baseline survey (questionnaire, weight and height, stool specimen) – before deworming |  |  |  |  |  | ✓ |  |  |  |  |  |  |  |  |
| Deworming |  |  |  |  |  | ✓ |  |  |  |  |  |  |  |  |
| Start of the education program in the intervention schools |  |  |  |  |  | ✓ | ✓ | ✓ | ✓ | ✓ |  |  |  |  |
| Cure rate estimation (2 weeks post-deworming) |  |  |  |  |  |  | ✓ |  |  |  |  |  |  |  |
| Second survey (questionnaire, weight and height, stool specimen) |  |  |  |  |  |  |  |  |  | ✓ |  |  |  |  |
| Training workshop of the education program offered to control schools |  |  |  |  |  |  |  |  |  | ✓ |  |  |  |  |
| Health education program offered to control schools |  |  |  |  |  |  |  |  |  | ✓ | ✓ | ✓ | ✓ |  |
| Data analysis |  |  |  |  |  |  |  |  |  |  | ✓ | ✓ | ✓ |  |
| Begin dissemination of results |  |  |  |  |  |  |  |  |  |  |  |  |  | ✓ |

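### The absenteeism window opens at baseline, before deworming and before the education starts, so any days in between would dilute the first secondary outcome; minor, and removable at almost no cost

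*Protocol*

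**What the plan says.** The absenteeism window is set in the protocol, Methods, Study design: "Absenteeism rates, based on routine school records, will be assessed from baseline to the end of the follow-up period". The same section ties the start of the education to deworming: "The health hygiene education intervention will begin immediately after the routine deworming program in schools in the intervention arm".

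The Chronogram of research activities gives the order of the first two events in its row label: "Baseline survey (questionnaire, weight and height, stool specimen) – before deworming". It ticks that survey in April 2010, deworming in April 2010, and the row "Start of the education program in the intervention schools" from April to August. The grid is monthly, and its introduction describes the schedule as one "with approximate start and end dates".

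Absenteeism heads the list of secondary objectives: "i) to determine intervention effects on absenteeism rates".

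**The concern.** Set side by side, these statements give the order baseline survey, deworming, education. An outcome window that opens at the baseline survey includes whatever school days fall before deworming. On those days no school has the education programme, so the two arms should differ only by chance. Counting them as follow-up averages a period without effect into the comparison and shrinks the estimated difference.

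At stake is the estimate for the first secondary objective. The title on the protocol's English questionnaire describes the intervention as education given after deworming, so days before deworming do not belong to the question being asked. Whether earlier absence records should serve as a covariate is a separate matter.

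**Working it through.** **Is there a planned figure to reproduce?** Not for absenteeism. The Sample size justification concerns re-infection only. Its figures reproduce closely:
- Participants: 1438 × 0.806 × 0.95 = 1101 (stated 1101).
- Design effect: 1 + (1101/18 − 1) × 0.028 = 2.68 (stated 2.7).
- Effective sample size: 1101/2.68 ≈ 410 (stated 412).
- Power at an odds ratio of 1.75 with 206 per arm: 79.6% (Wald) or 80.1% (pooled test of two proportions), against 80.3% stated.

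None of these figures depends on the absenteeism window, so none changes.

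**Inputs for the dilution**
- F, the time from the start of education to the end of follow-up: 4 months, about 17.4 weeks. The follow-up length is given under Study design, and the Health hygiene education intervention section has research visits "to monitor the application of the education program during the 4-month follow-up period".
- g, the gap from the baseline survey to the start of education: not stated, so an assumption. With all three events ticked in April, the range is 0 to about 4 weeks.
- e, the true relative reduction in absence while the education runs: not stated. The value of 25% below is only an illustration.

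**Assumptions.** The 4 months run from the start of education. School days are spread evenly over the weeks. The absence rate without education, r, is the same before and after deworming and in both arms. The effect is constant once education starts.

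**Formula.** Over the whole window the control rate is r. The intervention rate is r[g + F(1 − e)]/(g + F). The observed relative reduction is therefore e × F/(F + g), and the share of the effect lost is g/(F + g). If e is read as the average effect over the education period, the share lost is the same when the effect builds up gradually.

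| Gap g | Share lost, g/(17.4 + g) | A 25% reduction would appear as |
|---|---|---|
| 0 | 0% | 25.0% |
| 0.5 week | 0.5/17.9 = 2.8% | 24.3% |
| 1 week | 1/18.4 = 5.4% | 23.6% |
| 2 weeks | 2/19.4 = 10.3% | 22.4% |
| 3 weeks | 3/20.4 = 14.7% | 21.3% |
| 4 weeks | 4/21.4 = 18.7% | 20.3% |

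**Sensitivity to the assumptions.** The Scientific background reports a 25% fall in school absenteeism after deworming in another country. If the same fall occurred here, the pre-deworming days would carry more absences and weigh more. The share lost would be g/(0.75 × 17.4 + g): 1/14.05 = 7% at 1 week, 2/15.05 = 13% at 2 weeks and 4/17.05 = 23% at 4 weeks. If instead the 4 months ran from baseline, the share would be g/17.4: about 6%, 11% and 23% at the same gaps.

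**Does the calendar say anything about the gap?** Only weakly. The cure-rate assessment, due two weeks after deworming, is ticked in May alone. Taken at face value, that puts deworming of the children sampled for it no earlier than about 17 April. This leaves room for a gap but does not show one, because the dates are approximate and the survey days within April are not given.

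**The case against.** The strongest case on the other side is that nothing shows the gap to be material. Education follows deworming at once, all three events share one month, and a gap of a day or a few days per school fits the text. A gap of 4 weeks in every school would need all of them surveyed at the start of April and dewormed at its end. Schools are randomised in February, before baseline, so a window from baseline is the same in both arms and compatible with intention to treat. Baseline might mean the start of the trial period and not a survey day. The chronogram row "Training workshops for teachers in the intervention schools" is ticked for February and March, so the early days may not be wholly free of influence. The exact start day of a register-based secondary outcome could also be left to an analysis plan.

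Much of this stands: the size is unknown, it may be nil, and the direction is conservative. Three parts do not remove the point. First, the protocol does not leave the start open; it states it, and elsewhere in Study design baseline is the word for the questionnaire round. If something else was meant, naming the date settles it. Second, intention to treat decides which children are analysed in which arm; it does not require counting days before the intervention begins. Third, earlier teacher training does not move the start of the intervention, which Study design places after deworming.

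A reader might infer more than the documents support. They do not show that dilution has been built in at a known size, because no gap in days appears anywhere. They do not say that the baseline survey runs across the whole month or that the gap differs between schools. A loss of power cannot be quoted either, because the protocol gives no power, effect size or variance for absenteeism. Nor is there bias in favour of the intervention, since the same window applies to both arms.

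**Conclusion.** The point holds as a minor one about a rule the protocol states. As written, the absenteeism window includes any school days between the baseline survey and deworming, and those days are unexposed in both arms. The loss runs from 0% with no gap to at most about 19% of the effect with a 4-week gap, with about 5% at 1 week and 10% at 2 weeks. These figures rest on an assumed gap within April, 4 months of education after it, equal absence rates before and after deworming, and a constant effect. The two alternative assumptions tried raise the 4-week figure to about 23%. Any error is towards no effect and favours neither arm. The primary outcome, the sample size and every stated power figure are untouched. This is not a contradiction or an arithmetic error in the plan.

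**What to change.** In the protocol, Study design, replace the baseline start of the absenteeism window. Count absences from the first school day after each school's deworming to that school's 4-month survey, apply the same rule in intervention and control schools, and do not count earlier days as outcome time. Re-infection after deworming is compared in both arms, so a deworming date exists in every school and the rule keeps every child in the allocated arm.

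The cost is one sentence and a note of two dates per school. The registers are the same, no new data are needed, and only the days before deworming leave the outcome.
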